### Objectives to be explored in the RCT

- 1. To estimate the effect of a motor skills intervention on aberrant movement patterns and musculoskeletal health.

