### Objectives to be explored in the full cohort

1. To describe the age and sex related incidence and course of back-, neck- and extremity-disorders in a general paediatric population from three to fifteen years of age.
2. To establish potential patterns of development of musculoskeletal disorders from three to fifteen years of age.
3. To determine the potential relationship between poor motor performance and aberrant movement patterns.
4. To determine the potential relationship between motor performance at the end of preschool and musculoskeletal health throughout the school years.

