### Covariates

The following covariates will be accounted for when analysing the results: sex, age, socioeconomic status, child well-being and parental MSK health.

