### Analyses

Multilevel logistic regression will be conducted to determine if there was a difference in aberrant movement problems by intervention group after adjusting for time in intervention, imbalanced covariates from WP1, school and socioeconomic status of the school.

Multilevel Poisson regression will be conducted if the number of MSK diagnoses of persistent problems differs by intervention group after adjusting for time on intervention, imbalanced covariates from WP1, school and socioeconomic status of the school.

The age-specific, sex-specific and age- and sex-specific incidence rate of MSK conditions will be calculated.

Longitudinal latent class analysis and latent class growth analysis will be conducted to describe the MSK developmental patterns. The sequential model comparisons (T classes vs. T + 1 classes) and chi-square goodness-of-fit test will be evaluated using the parametric bootstrapping technique. Lastly, the associations between class membership and the prevalence of related measures will be examined using a confirmatory latent class analysis approach.

Multilevel longitudinal logistic regression analyses will be conducted to determine if poor motor performance is associated with aberrant movement patterns after adjusting for age, sex and other important covariates. The interaction between time and poor motor performance will be examined.

Multilevel longitudinal Poisson regression analyses will be conducted to determine if motor performance at the end of preschool is predictive of the number of MSK diagnoses throughout the school years after adjusting for age, sex and other important covariates. The interaction between time and motor performance will be examined.

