81. Compared to previously used methods using this method will likely improve compliance rates, improve the control of non-wear time and the quality of measurement since the accelerometer keeps the same position on the body and follows the movement of the body. This method has previously been applied in 900 Danish children 9-14 years of age (8).
82. The instrument will be attached to the body using skin-friendly and permeable adhesive patches. If the children participating in this project have eczema or other skin problems, they will be offered to wear an instrument in a belt.
83. We have previously used accelerometers to assess physical activity among large groups of children in this age-group (9-11). The monitors will be initialized to record data during six consecutive days in raw sampling format, which makes it suitable for detecting the short bursts of activity that are typical of preschool children. Sports participation will be obtained from school age using parental-reported SMS as described in WP 3 and previously obtained in the CHAMPS-DK study (12).
84. *Analysis plan*
85. Mixed model linear regression will be used to compare 3-year changes in physical activity and adiposity
86. between children in the intervention group and control group with appropriate adjustment for imbalanced
87. covariates and baseline levels of the outcomes. Bi-directional association between motor skills
88. development and change in physical activity and sports participation will be analyzed in a cohort approach
89. using mixed model regression with adjustment for experimental allocation group and other putative
90. determinants of motor skills and physical activity.
91. Annually obtained information on motor skills will be used to calculate percentile curves for motor skills
92. from age 3 to 5 years to illustrate the developmental course and provide age- and sex-specific variability in
93. a community-wide sample of apparently healthy children.
94. **Primary responsibility**
95. Associate [name] (Head of Research Unit for Exercise Epidemiology and Research in
96. Childhood Health), Department of Sports Science and Clinical Biomechanics, University of Southern
97. Denmark.
98. **References**
99. 1. Burgi F, Meyer U, Granacher U, Schindler C, Marques-Vidal P, Kriemler S, et al. Relationship of physical
100. activity with motor skills, aerobic fitness and body fat in preschool children: a cross-sectional and

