### Covariates

The following covariates will be accounted for when analysing the results: Sex, age, socioeconomic status, motor development.

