### Analyses

Cross-sectional analyses will be conducted using multilevel linear regression to determine the association between language and literacy skills and motor development after adjusting for age, gender and SES level.

Multilevel linear regression analysis will be used to determine the prediction from the early language and literacy measures, together with age, gender, and SES, to the three educational outcomes of Language comprehension, Decoding, Reading comprehension, taken from the National Test. The regression analysis determined the effect of age, sex and SES on mean levels of performance, as well as evaluating the unique variance contributed by early language, literacy motor performance and SES.

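### WP 4 adjusts its cohort association model for randomised allocation; WP 5 leaves allocation out of its stated adjustment sets and WP 3 does not name it, which allows a small, conditional bias.

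*Protocol*

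**What the plan says.** **WP 4, Analysis plan.** The bi-directional association between motor skills and physical activity or sports participation is analysed as a cohort, "using mixed model regression with adjustment for experimental allocation group and other putative" determinants. Allocation is named.

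**WP 3.** The motor-performance questions stand under the heading "Objectives to be explored in the full cohort", so both arms are pooled. The Analyses section gives two cohort regressions. The longitudinal logistic model asks whether "poor motor performance is associated with aberrant movement patterns after adjusting for age, sex and other important covariates". The longitudinal Poisson model asks whether "motor performance at the end of preschool is predictive of the number of MSK diagnoses throughout the school years after adjusting for age, sex", and that sentence ends with the same open reference to further covariates. The WP 3 Covariates section lists "sex, age, socioeconomic status, child well-being and parental MSK health". In the Analyses section, intervention group appears only in the two models for the randomised comparison.

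**WP 5.** The cross-sectional model examines the "association between language and literacy skills and motor development after adjusting for age, gender and SES level". The model for later reading uses early language and literacy measures with age, gender and SES, and evaluates the unique variance from several sources, motor performance among them. The Covariates section lists "Sex, age, socioeconomic status, motor development". No open clause is attached to either model.

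**Programme effects on the same outcomes.** WP 3 has as its trial objective "To estimate the effect of a motor skills intervention on aberrant movement patterns and musculoskeletal health". WP 5 has a parallel trial objective for language and pre-literacy.

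**The concern.** Motor performance at the end of preschool is measured after some of the cohort has been exposed to the programme, and the programme is meant to raise it. WP 5's second and third cohort objectives span ages three to six and three to fifteen, so they too are likely to draw on motor data collected after baseline.

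The protocol itself describes ways in which the programme could reach the outcomes without passing through measured motor skill. WP 4 makes physical activity and body composition trial outcomes, and both could plausibly affect musculoskeletal health. The WP 6 Background notes that, because the programme is built into the curriculum, it may alter how children interact with peers and staff. That is a plausible route to language.

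Where both links exist, allocation is a common cause of exposure and outcome. A pooled model without it credits part of the programme's effect to the child's own motor performance. WP 3 aims to identify targets for early prevention, so that attribution matters for interpretation. The randomised comparisons are not affected.

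**Working it through.** The protocol gives no figure to reproduce. The check has two parts: the adjustment sets side by side, and the size of the possible bias under assumed effects.

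**1. Adjustment sets of the cohort models**

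| Model | Stated adjustment | Allocation named? |
|---|---|---|
| WP 4, bi-directional association | allocation group and other determinants | yes |
| WP 3, logistic (movement patterns) | age, sex, unspecified others | no, but the set is open |
| WP 3, Poisson (MSK diagnoses) | age, sex, unspecified others | no, but the set is open |
| WP 5, cross-sectional language | age, gender, SES | no, and the set is closed |
| WP 5, later reading | early language and literacy, age, gender, SES, motor performance | no, and the set is closed |

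**2. Size of the bias in a rate-ratio model**

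Inputs, all assumed because the document gives none of them:
- equal allocation;
- δ, the programme effect on motor performance, in within-arm SDs: 0.2 to 0.5;
- RR, the programme's effect on the outcome by routes other than measured motor skill: 0.9 to 0.7;
- no true association between motor performance and the outcome within arm.

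With equal arms the allocation indicator has variance 1/4. Its covariance with motor performance is δ/4, and the pooled variance of motor performance is 1 + δ²/4. The bias in the log rate ratio per SD is therefore

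ln(RR) × (δ/4) / (1 + δ²/4).

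- δ = 0.2, RR = 0.9: −0.1054 × 0.05 / 1.01 = −0.0052, a factor of 0.995.
- δ = 0.3, RR = 0.8: −0.2231 × 0.075 / 1.0225 = −0.0164, a factor of 0.984.
- δ = 0.5, RR = 0.7: −0.3567 × 0.125 / 1.0625 = −0.0420, a factor of 0.959.

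The range is a shift of about 0.5% to 4% per SD.

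A simulated Poisson regression (400,000 children, true motor rate ratio 1.00) agrees:

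| δ | direct RR | without allocation | with allocation |
|---|---|---|---|
| 0.3 | 0.8 | 0.980 | 0.997 |
| 0.5 | 0.7 | 0.963 | 1.004 |
| 0.3 | 1.0 | 0.998 | 0.998 |
| 0.0 | 0.7 | 0.999 | 0.999 |

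The last two rows show that the bias vanishes when either link is missing.

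**3. Effect of the multilevel structure**

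For a continuous outcome with a programme effect of o SD, the spurious single-level correlation is about δ·o/4. It is 0.3 × 0.2 / 4 = 0.015 at the low end. At 0.5 and 0.3 it is 0.0375, or 0.036 after scaling by the pooled SDs. The protocol specifies multilevel models. If allocation is by preschool and preschool is a random intercept, much of the contrast between arms goes into that intercept. In simulations assuming 1,000 children in 20 or 40 preschools and an intraclass correlation of 0.05 for both variables, the spurious slope fell to 0.004 to 0.013.

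**The case against.** The strongest reply is that WP 3 does not exclude allocation. Both WP 3 cohort models end in an open clause, and filling it is ordinary work for an analysis plan. Nor do the Covariates sections prove exclusion: the WP 3 list omits intervention group although the WP 3 trial models use it, and the WP 5 list omits it although WP 5 has a trial objective. This stands. A reader might infer that the WP 3 associations will be run unadjusted for allocation; the text supports only that allocation is not named.

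It is also fair to say that WP 5 does not state which wave of motor data enters each model, that baseline motor measures are independent of allocation by randomisation, and that the reading model is built mainly around early language. The point is therefore limited to models using post-baseline motor data.

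The WP 3 Background argues that better motor performance itself prevents musculoskeletal problems. If that were the only route, there would be no confounding. But WP 4 and WP 6 describe other possible routes, so this cannot be assumed.

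Two further inferences are tempting but unsupported. One is a materially inflated false-positive rate. Figures of 7.5% to 20.6% against a nominal 5% arise only with 1,000 independent children in a single-level model; the multilevel simulations gave 5.2% to 7.3%. The other is that the bias always runs away from zero. If the programme raised motor skill but also raised injury exposure through more activity, a protective association would be pulled towards zero.

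**Conclusion.** The work packages are inconsistent. WP 4 adjusts for allocation, WP 5 states adjustment sets that leave it out, and WP 3 leaves it unnamed in an open set. Where motor performance is measured after the programme has started, the omission can bias the association. A bias requires both that the programme changes motor performance and that it affects the outcome by another route; without either one it is nil.

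Under the assumed effects the shift is about 0.5% to 4% in the rate ratio per SD, and less if preschool random effects absorb part of the contrast between arms. The direction depends on the signs of the two effects. The document does not support a claim that these associations are known to be confounded, or that their conclusions would be seriously wrong. This is a low-cost improvement to secondary, observational objectives.

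**What to change.** In WP 5, add allocation group as a fixed covariate to every association or prediction model that uses motor data collected after baseline. In WP 3, name allocation group explicitly among the further covariates of the longitudinal logistic and Poisson cohort models. Both then match WP 4. If it is left out of any of these models, give the reason.

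The variable is already held, so the cost is one degree of freedom and a line of text. If allocation acts only through motor skill, conditioning on it also loses a little precision and slightly magnifies any residual confounding, by a factor of about 1 + δ²/4: 1 + 0.09/4 = 1.0225 for δ = 0.3 and 1 + 0.25/4 = 1.0625 for δ = 0.5, so about 2% to 6%.

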**Perspectives**

The RCT has the potential to show the effect of a motor performance programme on specific movement patterns. Of equal importance, the project will bring new insights into the early phases of MSK problems, including how and why these problems arise and develop and the type of problems children from three to 15 years of age experience. Through this rich dataset, we will be able to identify and recognise risk patterns which are important for preventing future chronic MSK conditions. Together, this opens ‘a window of opportunity’ for implementing targeted prophylactic strategies with the potential to reduce the risk of current and future MSK injuries and their associated individual and societal burden.

38. motor skill difficulties in early childhood, it is important to closely examine the relationship between motor
39. skills and physical activity from this early stage of life. Understanding the relationship between the two
40. constitutes an essential element needed to inform health and educational authorities as to the reasons for
41. prioritizing motor skill-oriented activity in early childhood.
42. To date, the potential nature of the relationship between motor skills and physical activity in preschool-age
43. children has received little scientific attention. When reviewing the literature, it becomes readily apparent
44. that the majority of the results from past studies are based on cross-sectional data. Furthermore,
45. inconsistent and limited findings make it difficult to determine whether motor skills during early childhood
46. predict habitual physical activity or sports participation later in childhood (1-3). In fact, we are only aware
47. of one study examining the relationship between motor skills during the preschool years and physical
48. activity in later childhood that has used an objective measure of physical activity. This study found that
49. motor skills were unrelated to later physical activity; however, the study was very modest in size and had a
50. short follow-up period (9 months) (1). Randomized controlled trials carried out in the preschool setting
51. with the aim of improving motor skills in healthy preschool children have not examined short- or long-term
52. effects on physical activity (4-6). Thus, the evidence base currently available to understand the extent to
53. which poor motor skills acquisition in early childhood causes later physical inactivity is limited.
54. Another important and plausible consequence of poorly developed motor skills in early childhood is
55. obesity. Although this relationship to a large extent could be explained by habitually low physical activity, it
56. is important to establish the direct and indirect effects of motor skill development on obesity in early
57. childhood. The scientific evidence for this topic is also very limited, and randomized controlled trials and
58. appropriately sized cohort studies are warranted - this being another important reason for conducting this
59. project. Finally, because the sample in the current study is community-wide, it is a valuable source for
60. obtaining reference data on motor skills according to the MABC-2 motor skills test battery. Such reference
61. data is valuable for future surveillance and screening purposes. Thus, an additional aim of this WP is to
62. establish a population-based set of motor skill data to provide standards for interpreting values of motor
63. skills by age and sex.
64. **Objectives**
65. Collectively, the objectives of this WP are:
66. 1. To examine the effect of a three-year motor skills intervention program on short-term (<3-year)
67. changes in objectively measured physical activity and body composition in children attending preschool
68. 2. To examine the effect of a three-year motor skill intervention program in preschool children on longterm
69. changes in objectively measured physical activity and sports participation from preschool age to
70. preadolescence
71. 3. To elucidate the possible bi-directional association between motor skills and objectively measured
72. physical activity and sports participation during preschool and in preadolescence
73. 4. To establish population-based reference data on motor skills according to age and sex
74. **Variables**
75. The outcome measures for this WP are objectively measured physical activity and obesity. A description of
76. the methods to assess motor skills and body composition is provided in the main protocol.
77. *Assessment of physical activity*
78. Habitual physical activity will be assessed at baseline, and at 18 and 30 month.
79. Detailed, objective information on the whole spectrum of behaviours (from sleep-cycle to vigorous activity) will be assessed by continuous 24-hour/6 day Axivity® accelerometer measurement using simultaneous thigh and lower back positioned monitors. The method is an age adjusted version of the method used by Skotte et al. (2014) which provides the ability to classify postural allocations like sitting, lying and standing and activities like walking and running with high sensitivity and specificity (7).
80. The Axivity® AX3 monitor is a small (23 x 32.5 x 7.6 mm), lightweight (11 g), waterproof, 3-axis accelerometer data logger (Axivity, 2016). The monitors will be attached on the child´s right thigh and to the right on the lower back using an allogenic adhesive patch to enable full 24-hour recordings.
81. Compared to previously used methods using this method will likely improve compliance rates, improve the control of non-wear time and the quality of measurement since the accelerometer keeps the same position on the body and follows the movement of the body. This method has previously been applied in 900 Danish children 9-14 years of age (8).
82. The instrument will be attached to the body using skin-friendly and permeable adhesive patches. If the children participating in this project have eczema or other skin problems, they will be offered to wear an instrument in a belt.
83. We have previously used accelerometers to assess physical activity among large groups of children in this age-group (9-11). The monitors will be initialized to record data during six consecutive days in raw sampling format, which makes it suitable for detecting the short bursts of activity that are typical of preschool children. Sports participation will be obtained from school age using parental-reported SMS as described in WP 3 and previously obtained in the CHAMPS-DK study (12).
84. *Analysis plan*
85. Mixed model linear regression will be used to compare 3-year changes in physical activity and adiposity
86. between children in the intervention group and control group with appropriate adjustment for imbalanced
87. covariates and baseline levels of the outcomes. Bi-directional association between motor skills
88. development and change in physical activity and sports participation will be analyzed in a cohort approach
89. using mixed model regression with adjustment for experimental allocation group and other putative
90. determinants of motor skills and physical activity.
91. Annually obtained information on motor skills will be used to calculate percentile curves for motor skills
92. from age 3 to 5 years to illustrate the developmental course and provide age- and sex-specific variability in
93. a community-wide sample of apparently healthy children.
94. **Primary responsibility**
95. Associate [name] (Head of Research Unit for Exercise Epidemiology and Research in
96. Childhood Health), Department of Sports Science and Clinical Biomechanics, University of Southern
97. Denmark.
98. **References**
99. 1. Burgi F, Meyer U, Granacher U, Schindler C, Marques-Vidal P, Kriemler S, et al. Relationship of physical
100. activity with motor skills, aerobic fitness and body fat in preschool children: a cross-sectional and

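### WP 4 does not exclude intervention-exposed measurements from the MABC-2 reference percentile curves, so a working intervention would push the screening norms upward

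*Protocol*

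**What the plan says.** WP 4 sets out to "establish a population-based set of motor skill data to provide standards for interpreting values of motor" skills by age and sex, and this is its fourth objective. The Background section explains why the trial sample is thought suitable: "because the sample in the current study is community-wide, it is a valuable source for" reference values on the MABC-2. It adds that such "data is valuable for future surveillance and screening purposes".

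The Analysis plan then names the data: "Annually obtained information on motor skills will be used to calculate percentile curves for motor skills", running "from age 3 to 5 years to illustrate the developmental course and provide age- and sex-specific variability in" "a community-wide sample of apparently healthy children". The sentence does not mention allocated group, baseline or follow-up.

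The sentence directly before it concerns the two-way association between motor skills and physical activity. It is analysed "using mixed model regression with adjustment for experimental allocation group and other putative" determinants, so allocation is handled there.

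WP 1 (Variables) makes the MABC-2 at 18 months the primary outcome. By then the intervention children have had 12 months of the programme after a six-month phase-in. The WP 4 objectives call the programme a three-year one.

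**The concern.** A reference curve used for screening should describe children like those who will be screened. Here they are children who have not been through this programme. Yearly measurements of the trial sample include follow-up scores from children trained in the very skills being measured. If those scores enter the curves and the training works, the curves describe a mixture of exposed and unexposed children and lie above the unexposed population. Unexposed children elsewhere would then be labelled as having poor motor skills more often than the nominal centile implies.

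The shape of the curves is also at risk. A child's exposed measurements always come at an older age than the same child's baseline, so the exposed share would tend to rise from age 3 to age 5. The upward shift would then grow with age and be read as normal development, which the curves are meant to show.

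**Working it through.** The document gives no sample size, effect size, SD or allocation ratio for this point, so there is no stated figure to reproduce. The calculation below is an illustration on assumed inputs.

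**Inputs**
- From the document: the data source (yearly measurements, trial sample), the age range 3 to 5, and the MABC-2 as both primary outcome and reference instrument.
- Assumed: effect d from 0 to 0.5 SD; share p of the measurements at a given age that come from exposed children, 0.25 to 0.50; normal scores with equal SD in exposed and unexposed children.
- Assumed as cut-offs: the 5th and 15th centiles. The document sets none.

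**Method**
1. Scale the unexposed scores to N(0, 1). The pooled reference distribution is then (1 − p)·N(0, 1) + p·N(d, 1).
2. For a nominal centile c, solve (1 − p)·Φ(x) + p·Φ(x − d) = c for x.
3. The shift is x − Φ⁻¹(c). The share of unexposed children below the published centile is Φ(x).

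**One case by hand.** Take d = 0.3, p = 0.5, c = 0.05. The solution is x = −1.513. Check: 0.5·Φ(−1.513) + 0.5·Φ(−1.813) = 0.5·0.0651 + 0.5·0.0349 = 0.0500. The shift is −1.513 + 1.645 = 0.132 SD, and Φ(−1.513) = 6.5% of unexposed children fall below the curve labelled 5th.

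**Results**

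| d (SD) | p | Shift at 5th / 15th (SD) | Unexposed below nominal 5th | Unexposed below nominal 15th |
| --- | --- | --- | --- | --- |
| 0 | any | 0 / 0 | 5.0% | 15.0% |
| 0.2 | 0.25 | 0.044 / 0.046 | 5.5% | 16.1% |
| 0.2 | 0.50 | 0.092 / 0.095 | 6.0% | 17.3% |
| 0.3 | 0.33 | 0.083 / 0.089 | 5.9% | 17.2% |
| 0.3 | 0.50 | 0.132 / 0.138 | 6.5% | 18.5% |
| 0.5 | 0.50 | 0.199 / 0.217 | 7.4% | 20.6% |

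At the 5th centile, the rows with d from 0.2 to 0.5 give between 5.5/5 = 1.10 and 7.4/5 = 1.48 times the nominal number of unexposed children flagged. With exposed measurements removed, p = 0 and the shift is zero at every centile, whatever d is.

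**The case against.** **The text never says that all measurements from both arms are pooled.** A reader might infer that the plan prescribes this. It does not: the reading comes from yearly data, a community-wide sample and the absence of any restriction. WP 4 sends the description of motor-skill assessment to a main protocol that is not among the documents, and a restriction could stand there. Allocation is known, so the analyst can still restrict the sample without changing data collection. This stands as a limit on how firmly the point can be put. It does not remove the point, because the WP 4 text already names the data source and, followed as written, lets exposed scores in.

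**It could be left to the analysis plan.** The smoothing method could. Which children make up the reference population is the substance of objective 4, and the protocol has addressed it.

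**The larger figures are at the high end.** This is fair. Under 1:1 allocation, which is itself not stated, p = 0.5 would need every measurement at that age to be post-baseline. WP 1 gives a follow-up of 6 to 30 months ending when the child leaves preschool. That suggests children enter at different ages, so baseline scores probably contribute at older ages too and lower p.

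**A reader might extend the point to WP 3 and WP 5.** The documents do not support that. The WP 3 cohort models leave room for further important covariates, which can include allocation. WP 5 plans "multilevel linear regression to determine the association between language and literacy skills and motor development after adjusting for age, gender and SES level", without an allocation term, but does not say at which visit. At baseline, allocation is irrelevant. Later, a randomised allocation that affects language only through motor skills does not confound the association. An omitted covariate is also a different problem from a shifted norm, and the figures above say nothing about it.

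**Conclusion.** The point holds for the WP 4 reference curves alone. As written, the plan does not keep intervention-exposed measurements out of norms intended for unexposed children, although the adjacent analysis in the same section takes allocation into account.

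The direction follows from any positive effect: the norms come out too high. The size is conditional on the assumed d and p. It is zero if the programme has no effect, small for a modest effect with a quarter of measurements exposed, and close to half as many again below the 5th centile at the top of the assumed range. That the shift grows with age is a tendency, since the spread of ages by visit is not given.

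The trial's primary comparison does not depend on these curves and is unaffected. The matter should be corrected before any norms are published, but it does not threaten the trial's main result.

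**What to change.** Add one sentence to the WP 4 Analysis plan defining the reference sample, for example: the percentile curves use baseline measurements of all children and follow-up measurements of children in control preschools only. If the main protocol already says this, a cross-reference is enough.

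An alternative that discards no data is to present the curves by allocation group, with the unexposed curve as the reference and the pooled curve only as a sensitivity analysis.

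No new data are needed. The cost of the restriction is the intervention group's post-baseline measurements, hence wider uncertainty at the oldest ages. How much is lost depends on the allocation ratio and the ages at each visit, which the document does not give.
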